## Materials and methods

### Study design

This protocol, which adheres to the SPIRIT 2013 guidelines (see S1 File), describes the Dino Study (Daily Intervention-based research on Nurturing Opportunities), a two-arm randomized controlled trial (RCT) designed to evaluate the effectiveness of the IY Small Group Dinosaur Child Program in Dutch children aged 4–8 years with perceived elevated or (sub)clinical levels of conduct problems [20,21,24]. A total of 120 children and one primary caregiver per family will be enrolled and randomly assigned to either an intervention group (n = 60) or a waitlist control group (n = 60), using a 1:1 ratio. The study assesses both group-level effects and individual variability in treatment response by analyzing intensive longitudinal data (ILD) from daily diaries to capture children’s moment-to-moment negative affect, externalizing behaviors, and daily parent–child interactions. The intervention group will receive the Dinosaur Child Program in small groups across 18 weekly sessions. The control group will receive care-as-usual and will be offered the intervention after posttest assessment. Pretest (T1) and posttest (T2) assessments will be conducted using standardized questionnaires and a brief child interview, with T2 scheduled 19 weeks after T1. In addition, daily diary data on children’s emotional states, behavior problems, and parent–child interactions will be collected via the m-Path application [26] during a one-week baseline period, the 18-week intervention, and a one-week follow-up (i.e., 20 weeks total). Parent and child will complete the diary jointly each evening (Fig 1). Eligibility criteria include: (a) child age between 4 and 8 years at the start of the study (September 2025), (b) parental indication that the child shows elevated or (sub)clinical levels of conduct problems in daily life (e.g., frequent defiance, aggression, or rule-breaking behavior), (c) daily contact between the child and the participating parent, and (c) sufficient fluency in Dutch. Children are excluded if they have an intellectual disability (IQ < 70) or insufficient Dutch language proficiency.

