### Recruitment

Participants will be recruited from primary schools as well as preventive and clinical settings in collaboration with two mental health institutions. Information will be shared via email, school newsletters, posters, and individual consultations. Schools previously engaged in the IY training network will be prioritized. Parents who express interest will complete an online registration form and subsequently participate in a video call with trained research staff, who will confirm eligibility and provide detailed information about the study. During this call, digital informed consent will be obtained from parents or legal guardians. When appropriate, children will accompany this call and be given age-appropriate information and asked to provide verbal or digital assent. Participants will have the opportunity to ask questions and may withdraw from the study at any time without consequence.

Approximately one month prior to the intervention, families will receive a home visit to establish rapport and conduct baseline procedures. In the intervention group, this visit will be conducted by the child’s future group leader; in the control group, by a trained research assistant. During the visit, children will provide oral assent and complete a brief, age-appropriate interview. Parents will complete baseline questionnaires and receive instructions for installing the m-Path app [26]. An overview of participant flow, including enrollment, randomization, and assessment timing, is shown in Fig 2.

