### Power analysis

At the between-person level, an a priori G*Power analysis [27] indicated that 64 participants per group are required to detect a medium effect size (Cohen’s *d* = 0.5), and 26 per group for a large effect size (*d* = 0.8), assuming α = 0.05 and statistical power of 0.80. Previous studies of the IY Dinosaur Child Program have reported effect sizes between 0.70 and 0.81 for improvements in social competence [19], supporting the planned sample size of 120 to allow for potential attrition.

To evaluate intervention effects on intra-individual and dyadic dynamics via daily diaries, simulation-based power calculations were performed. These simulations examined time by condition (intervention vs. control) interactions in multilevel models, with rolling-window correlations nested within participants/families [28]. With 140 time points per child/ family (i.e., 7 days * 20 weeks), statistical power is expected to exceed 80% for detecting small interaction effects (β = 0.005).

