#### Timeline.

Participant recruitment will start in August 2025 and is expected to be completed by October 3, 2025. Intake interviews—including eligibility screening, explanation of the study procedures, and digital informed consent—will take place between September 1 and October 3, 2025, via scheduled video calls. Baseline assessments (T1), including home visits, parent questionnaires, and child interviews, will occur between September 15 and October 17, 2025. The intervention is scheduled to begin in the week of October 20, 2025, and will continue for 18 sessions through the week of March 9, 2026. Posttest assessments (T2), including follow-up home visits and questionnaires, will be conducted between March 16 and April 17, 2026. This timeline ensures a 5-week pretest period, an 18-week intervention period, and a 5-week posttest window. Study results are expected to be available by September 2026 and will be submitted for publication, presented at conferences, and reported in ClinicalTrials.gov.

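### The stated 19-week T1–T2 interval, 18-week program and 20-week (140-day) diary do not fit the protocol's own calendar, and late T1 visits may leave less than the stated baseline week

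*Protocol article*

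**What the plan says.** The protocol article describes the schedule in two ways.

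**As durations.** Study design gives the pretest-to-posttest interval as "with T2 scheduled 19 weeks after T1" and has the diary run "during a one-week baseline period, the 18-week intervention, and a one-week follow-up (i.e., 20 weeks total". Power analysis builds on the same count: "With 140 time points per child/ family (i.e., 7 days * 20 weeks". The Intervention section describes 18 sessions held once a week, and Data collection and procedures describes diary completion every evening through all three phases. No section mentions a break in the sessions or a pause in the diary.

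**As dates.** In the Timeline section, T1 (home visits, questionnaires, child interviews) "will occur between September 15 and October 17, 2025". The sessions start in the week of 20 October 2025 and "will continue for 18 sessions through the week of March 9, 2026". T2 assessments "will be conducted between March 16 and April 17, 2026". The section then sums up: "This timeline ensures a 5-week pretest period, an 18-week intervention period, and a 5-week posttest window".

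The diary app is set up at the T1 home visit. Recruitment says of that visit: "Parents will complete baseline questionnaires and receive instructions for installing the m-Path app". The same section places the visit about a month ahead of the intervention, and Data collection and procedures dates T1 to September 2025. The Timeline allows T1 until 17 October, the Friday before the first session week.

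**The concern.** The two descriptions cannot both be followed, and the trial relies on the figures that disagree: when T2 takes place, when the diary stops, and how many time points the power statement for the diary analyses assumes.

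The diary is where this matters most. Hypotheses 2 and 3 compare trajectories over the whole program, so the final session weeks and the week after the program are informative. If the app is programmed to stop after 20 weeks, those evenings are lost and cannot be collected later.

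The start of the diary matters too. Hypothesis 3 uses fluctuation in negative affect before the intervention as its moderator, and the section on child emotional variability computes variability as a within-person standard deviation. That quantity is less reliable from a few evenings than from a full week.

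**Working it through.** **Inputs** (all from the protocol article): T1 from Mon 15 Sep to Fri 17 Oct 2025; sessions from the week of Mon 20 Oct 2025 to the week of Mon 9 Mar 2026; T2 from Mon 16 Mar to Fri 17 Apr 2026 (Timeline). 19-week interval; diary of 1 + 18 + 1 weeks (Study design). 140 time points (Power analysis).

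**1. The plan's own figures.** The durations agree with each other: 1 + 18 = 19 weeks; 1 + 18 + 1 = 20 weeks; 7 × 20 = 140 days. As dates, this means a baseline week of 13–19 Oct, 18 consecutive session weeks from 20 Oct with the last beginning 16 Feb, and a follow-up week of 23 Feb–1 Mar. The Timeline does not give these dates.

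**2. T1-to-T2 interval from the Timeline.**
- Shortest, 17 Oct to 16 Mar: 150 days; 150 / 7 = 21.4 weeks.
- Longest, 15 Sep to 17 Apr: 214 days; 214 / 7 = 30.6 weeks.
- First to first, or last to last: 182 days; 182 / 7 = 26.0 weeks.
- T1 + 19 weeks falls between 26 Jan and 27 Feb 2026, before the T2 window opens and before the last session week.
- Counting from the first session week does not help: 20 Oct to 16 Mar is 147 days; 147 / 7 = 21 weeks.

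No pair of dates gives 19 weeks.

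**3. Length of the session period.** 20 Oct to 9 Mar is 140 days, or 20 weeks from first Monday to last Monday, so 21 calendar weeks inclusive. The excess over 18 is 3 weeks. Whole-week counting reproduces the Timeline's two 5-week windows (33 days each; 33 / 7 = 4.7), so the counting convention does not explain the difference.

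**4. Diary.**
- *If 20 weeks / 140 consecutive days governs:* 13 Oct + 139 days = 1 Mar 2026. The session weeks of 2 and 9 Mar and the follow-up week of 16–22 Mar are not covered. A diary started on the last T1 day, 17 Oct, ends on 5 Mar, still before the week of 9 Mar.
- *If the phases govern* (one week before the first session week to one week after the last): 13 Oct to 22 Mar inclusive = 161 days; 161 / 7 = 23 weeks. The excess over 140 is 21 days.

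The diary payment in Data collection and procedures fits the longer period somewhat better: 0.15 × 140 = EUR 21.00; 0.15 × 161 = EUR 24.15; the stated sum is about EUR 25. Because that sum is approximate, this is supporting evidence only.

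**5. Baseline week.** Seven evenings before Monday 20 Oct require app set-up by 13 Oct. A visit on 17 Oct leaves 3 evenings (17, 18, 19 Oct) before a Monday session, and 7 (17–23 Oct) before a Friday session on 24 Oct. Intake and consent run to 3 Oct, 17 days before 20 Oct, so families who consent late cannot have a visit a month ahead.

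**The case against.** The strongest reply is that this is one discrepancy seen from several sides. The durations agree among themselves; most of the conflict comes from the Timeline's end date, which adds three unexplained weeks. Those may be holiday weeks, and the schedule figures and the supporting files, which are not available here, may show them. This is fair as to cause. It does not remove the contradiction, because the Timeline itself still calls the period 18 weeks and the text mentions no breaks. Nor would it rescue the 19 weeks, since the Timeline's T1 and T2 windows exclude that interval anyway.

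Four stronger readings are tempting and are not supported.

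- *That the diary will contain no post-program data.* The article also defines the diary by phase, with a follow-up week after the intervention. Follow-up is lost only if the 20-week count is what gets implemented.
- *That the baseline week is generally missing.* Only visits after about 13 October are affected, the loss depends on the group's session day, and the Recruitment section intends visits about a month ahead. The hypothesis 3 moderator is defined as fluctuation before the intervention, not as a seven-day quantity.
- *That hypothesis 1 is biased.* The 21.4-to-30.6-week range pairs opposite ends of the two windows; families visited in the same order at both waves would all be near 26 weeks. Nothing says the windows differ by arm, and variation that is equal across arms adds noise, not bias. Adjusting for the interval would condition on a post-randomization variable and is not recommended here.
- *That diary power is overstated.* A 161-day diary would give more time points than the 140 assumed, and that would not by itself lower power.

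**Conclusion.** The contradiction is established from the protocol article's own dates. T2 falls 21.4 to 30.6 weeks after T1, about 26 if visit order is kept, against the stated 19. The session period is 21 calendar weeks against the stated 18. The 20-week count and the phase definition of the diary differ by 21 days, so one of them has to give way.

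Two consequences are conditional. The last session weeks and the follow-up week go unrecorded only if the 20-week count governs and the 140 days are consecutive, as daily completion without a stated pause implies. The baseline falls short of seven evenings only for families visited after about 13 October, with three evenings as the extreme case before a Monday session.

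Confidence is high for the date arithmetic and lower for how the schedule will be run. The point should be corrected before recruitment, which had not begun at this protocol version, because missed diary evenings cannot be recovered.

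**What to change.** Reconcile Study design, Recruitment, Power analysis, Data collection and procedures, Timeline and Intervention. No view is taken here on the session schedule itself.

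- Define diary start and stop by each group's actual first and last session: from 7 days before the first to 7 days after the last, with the same calendar dates for control families.
- Book T1 home visits so that at least 7 diary evenings precede the first session.
- State T2 as a window after the last session, applied in the same way in both arms.
- Replace the 19 weeks, the 20 weeks and the 140 time points with the figures that follow.

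The cost is protocol wording, the app's end date and the order of T1 bookings. The downside is up to about three more weeks of diary burden for families. At EUR 0.15 per entry, 161 entries come to EUR 24.15, which the stated allotment of about EUR 25 would cover.

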**Fig 1 pone.0330597.g001:**
[figure not shown]
SPIRIT schedule of enrollment, interventions, and assessments in the Dino Study. This figure presents a structured overview of study procedures and assessment timepoints, including enrolment, group allocation, intervention delivery, and outcome assessments. It displays which constructs were measured, by whom (parent, teacher, child), and when (T1 pretest, T2 posttest), and links each measure to the corresponding research question. Daily diary measures are also included to capture within-family processes during the intervention period.

### Recruitment

Participants will be recruited from primary schools as well as preventive and clinical settings in collaboration with two mental health institutions. Information will be shared via email, school newsletters, posters, and individual consultations. Schools previously engaged in the IY training network will be prioritized. Parents who express interest will complete an online registration form and subsequently participate in a video call with trained research staff, who will confirm eligibility and provide detailed information about the study. During this call, digital informed consent will be obtained from parents or legal guardians. When appropriate, children will accompany this call and be given age-appropriate information and asked to provide verbal or digital assent. Participants will have the opportunity to ask questions and may withdraw from the study at any time without consequence.

Approximately one month prior to the intervention, families will receive a home visit to establish rapport and conduct baseline procedures. In the intervention group, this visit will be conducted by the child’s future group leader; in the control group, by a trained research assistant. During the visit, children will provide oral assent and complete a brief, age-appropriate interview. Parents will complete baseline questionnaires and receive instructions for installing the m-Path app [26]. An overview of participant flow, including enrollment, randomization, and assessment timing, is shown in Fig 2.

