### Randomization

This single-blinded RCT uses a randomized allocation procedure with a 1:1 allocation ratio to assign participants to either the intervention or waitlist control group. An independent researcher will generate the random allocation sequence using a computer-based random number generator. The personnel responsible for enrolling participants and assigning them to interventions will not have access to the random allocation sequence until after the baseline assessment is completed, at which point parents will be notified of the group assignment.

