### Trial registration

The protocol of this study is registered at ClinicalTrials.gov with identification number NCT07051642 on July 9^th^, 2025. Protocol version 1, date 09.07.2025. The first participant has not yet been recruited. Additional details about the trial registration are presented Table 1.

**Table 1 pone.0330597.t001:** Overview of measurements.

Data category	Information
Primary registry and trial identifying number	ClinicalTrials.gov
	NCT07051642
Date of registration in primary registry	July, 9th, 2025
Secondary identifying numbers	TSB_RP2172
Contact for public queries	[name] e-mail: [contact]
Contact for scientific queries	[name] e-mail: [contact]
	Tilburg University, Tilburg, The Netherlands
Scientific title	The Dino Study: Rationale and study protocol for a randomized controlled trial evaluating the Incredible Years Dinosaur Program with daily assessments
Countries of recruitment	The Netherlands
Health condition(s) or problem (s) studied	Behavior problems in children, parent-child relations, oppositional behavior, executive functioning, and social and language skills
Intervention(s)	Active comparator: Incredible Years Dinosaur Program
	Control group: Waitlist control condition
Key inclusion and exclusion criteria	Ages eligible for study: child, adult, older adult
	Sexes eligible for study: both
	Accepts healthy volunteers: yes
	Inclusion criteria: Dutch-speaking children aged 4–8 years, at least one Dutch-speaking parent willing and able to participate in the study
	Exclusion criteria: intellectual disability in the child (IQ < 70), child lives primarily in a different household during weekdays, parent or child does not have sufficient Dutch language proficiency
Study type	Interventional
	Allocation: randomized, 1:1 assignment
	Masking: single (outcome assessor)
	Primary purpose: treatment
	Phase: not applicable
Estimated study start date	September 2025
Estimated primary completion date	April 2026
Target sample size	120
Recruitment status	Not yet recruiting
Primary outcome(s)	Change in social competence (parent and teacher reports) Change in externalizing behavior (parent and teacher reports) Change in executive functioning (parent and teacher reports) Change in language and communication skills (parent reports) Change in child-assessed emotion understanding and problem solving
Secondary outcome(s)	Daily dynamic emotional processes (ILD-based)
	Daily behavioral processes within families (Dyadic ILD-based)

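### The T1 home visit is staffed by arm, which conflicts with withholding allocation until baseline is complete and ties the T1 examiner to arm; the outcome-assessor masking label does not hold for parent-rated primary outcomes.

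*Protocol article*

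**What the plan says.** **The visit.** The Recruitment section says that about a month before the intervention "families will receive a home visit to establish rapport and conduct baseline procedures". It then assigns the visitor by arm: "In the intervention group, this visit will be conducted by the child’s future group leader; in the control group, by a trained research assistant". Data are collected at this visit. For children: "During the visit, children will provide oral assent and complete a brief, age-appropriate interview". For parents: "Parents will complete baseline questionnaires and receive instructions for installing the m-Path app". The Timeline makes the visit part of T1: "Baseline assessments (T1), including home visits, parent questionnaires, and child interviews, will occur between September 15 and October 17, 2025".

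**Allocation.** The Randomization section says that staff who enrol and assign participants "will not have access to the random allocation sequence until after the baseline assessment is completed", and that parents learn their arm at that point.

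**Masking.** The same section opens with "This single-blinded RCT uses a randomized allocation procedure". Table 1 under Trial registration gives "Masking: single (outcome assessor".

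**Mode of data collection.** Data collection and procedures has parents and teachers fill in T1 questionnaires online. It lists the home visit content as assent, a short emotion regulation task and app set-up.

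**Analysis.** Under Hypothesis 1, latent change score models test condition as a predictor of change from T1 to T2, separately for parent, teacher and child measures.

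**The concern.** Two statements about the same weeks do not fit together. One makes the T1 visitor depend on the child's arm. The other says the arm is released only once T1 is finished.

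Three things are at stake.

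- **Measurement.** Examiner type is fully confounded with arm at T1. A group leader building rapport with a future group member may elicit different answers from a research assistant. Any such difference enters the baseline from which change is measured. The Preliminary analyses section adds significant baseline differences as covariates, so a measurement artefact would be handled as if it were chance imbalance.
- **Expectation and loss.** A visitor who is the future group leader can reveal the arm to the family. That could colour parent-reported T1 scores, or lead to withdrawal before T1 that differs by arm.
- **Reporting.** A trial described as masking its outcome assessors, when many primary outcomes are rated by parents who know the arm, would be read as stronger evidence than it is.

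**Working it through.** **1. Order of events.** Set side by side:

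- Recruitment: the visitor is the future group leader in one arm and a research assistant in the other.
- Timeline: home visits and child interviews are T1, 15 September to 17 October 2025.
- Randomization: no access to the sequence for enrolling and assigning staff, and no notice to parents, until baseline is complete.

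To send a child's future group leader, whoever arranges the visit must know that child's arm. The visit is itself part of T1. Allocation is therefore known to someone before T1 is complete, and the visitor's role can disclose it before the stated notification point. Intake calls run from 1 September to 3 October, so from 15 September to 3 October visits that reveal the arm can take place while enrolment is still open.

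**2. Which measures are exposed.** Primary measures in the Outcome measures section, not counting the ECBI, which is described as a complement to the CBCL:

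| Rater | Measures | Link to T1 visitor | Masking at T2 |
|---|---|---|---|
| Parent (4) | CBCL, P-COMP, BRIEF-2 parent, CCC-2-NL | Indirect: completed online, but family may learn the arm | Not masked: parents have been told the arm |
| Teacher (3) | TRF, T-COMP, BRIEF-2 teacher | None stated | Not stated |
| Child (2) | Wally Feeling, Wally Problem Solving | Direct if given at the visit, which is probable but not stated outright | Visitor and coder not stated |

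**3. What a T1-only shift does.** The plan gives no figure on this point to reproduce. Its sample sizes of 64 and 26 per group do reproduce (63.77 and 25.52, rounded up, two-sided t-test), and nothing here depends on them.

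Let there be no true effect, a within-arm SD of 1 at both times, and a shift of b SD at T1 in the intervention arm only.

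- Difference in change between arms = [μ − (μ + b)] − [μ − μ] = −b. The full shift enters, with its sign reversed.
- SD of change = √(2(1 − r)), where r is the pre-post correlation.
- If T2 is instead adjusted for T1, the bias is r × b in size and the residual SD is √(1 − r²).
- Standard error factor with 60 per arm: √(2/60) = 0.183.

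Example, r = 0.5 and b = 0.2: the SD of change is 1, and 0.2/0.183 = 1.10 standard errors, so a two-sided 0.05 test rejects about 19.5% of the time. With adjustment the bias is 0.10 and the residual SD 0.866; 0.10/(0.866 × 0.183) = 0.63 standard errors, which rejects about 9.7% of the time.

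| r | b (SD) | Bias in change | Rejection rate | Bias, T1-adjusted | Rejection rate |
|---|---|---|---|---|---|
| 0.5 | 0.1 | 0.10 | 8.5% | 0.05 | 6.2% |
| 0.5 | 0.2 | 0.20 | 19.5% | 0.10 | 9.7% |
| 0.5 | 0.3 | 0.30 | 37.6% | 0.15 | 15.8% |
| 0.3 | 0.2 | 0.20 | 15.2% | 0.06 | 6.4% |
| 0.7 | 0.2 | 0.20 | 29.3% | 0.14 | 18.9% |

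Both b and r are assumptions; the document gives neither. The rates use a normal approximation and an unadjusted 0.05. The planned Bonferroni threshold would lower them but would leave the bias unchanged.

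**The case against.** **The concealment rule is narrower than it looks.** It binds staff who enrol and assign. Consent and eligibility are settled on a video call before the home visit, so a visitor who knows the arm need not break the rule for those staff. This stands in part. A reader might infer that concealment at enrolment has failed and that selection bias follows; the document does not show that, and enrolment of each child may well be concealed. What cannot be reconciled is arm-specific staffing of T1 with parents learning their arm only afterwards, and with an allocation withheld until baseline is complete. The participant flow figure, which shows the timing of randomization, is not available here.

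**The visitor does not touch every outcome.** This stands. It would be tempting to say that every Hypothesis 1 outcome carries examiner bias. Parent and teacher questionnaires are completed online, and teacher scores have no stated link to the visit. A direct examiner effect is plausible mainly for the child interview, and that the Wally tests are given there is an inference.

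**Masking is not shown to fail everywhere.** This also stands. For teachers, T2 visitors and Wally coders the document is silent, and an article may leave such detail to the full protocol. Nor can one say that parents shape every diary outcome: diary completion is described as joint in Study design and for the RQ2 items, but as independent for parent and child in the RQ3 items. Unmasked parent rating is unavoidable in a waitlist trial, so the remedy there is wording.

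**The size of the bias is assumed.** Correct. The shift might be zero. If T2 visits were staffed in the same way and produced the same shift, it would cancel from the change score; the T2 visitor is not named.

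**Conclusion.** The point holds in two parts.

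First, the Recruitment and Randomization sections describe incompatible procedures for T1. If Recruitment is followed, T1 examiner is confounded with arm, most directly for the child interview, and families may learn their arm before baseline is complete. Early knowledge could also affect parent-reported T1 scores or withdrawal before T1. A T1-only shift of b SD passes in full into the change contrast; adjustment for T1 reduces it to r × b. The tabulated rejection rates show how the problem scales under assumed b and r. They are not an estimate for this trial, because the size and direction of b are unknown.

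Second, the masking label is wrong for the four parent-rated primary measures, because parents are told their arm before T2. For the three teacher measures and the two child tests it is unsupported, not disproved.

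This needs correcting before T1 begins, since affected baseline scores cannot be collected again. The article states that no participant had yet been recruited.

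**What to change.** - Complete all T1 measures before a child's allocation is released. Draw T1 visitors from the existing research assistants and group leaders without regard to arm.
- Move the group leader's rapport contact to after T1 and allocation.
- Have the child tests scored by coders unaware of arm, and state who makes the T2 visits.
- In the Randomization section and Table 1, limit the masking statement to the measures it covers and say that parents are unblinded.
- If visit staffing cannot change, say plainly that T1 is post-allocation and unmasked, and amend the concealment statement to match.

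**Cost.** A change to the visit rota and to protocol and registry wording. The document does not give the number of research assistants, so capacity needs checking. The downside is timing: T1 runs to 17 October and sessions start in the week of 20 October, so the last-assessed families would have only a few days for the leader's contact.
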